## Abstract

**Background:**

Pregnancy is a complex period involving significant physical, mental, and social changes in a woman’s life, affecting her psychological well-being. According to the literature, anxiety, stress, and depression are common symptoms among pregnant women. Promoting a healthy lifestyle with a focus on mental health is essential. In this context, digital solutions such as coaches on smartphones are emerging as valuable tools to support the psychological well-being of pregnant women without existing disorders.

**Objective:**

This study aims to present the research protocol of a pilot study designed as a proof-of-concept investigation. The study evaluates the feasibility, acceptability, and utility of an acceptance and commitment therapy–based stress management mobile app. The primary objective is to explore the feasibility of using a coach, ALBA (A Well-Being Assistant), developed within the TreC Ricerca app, to promote women’s psychological well-being during pregnancy through 5 sessions based on acceptance and commitment therapy. The pre- and postintervention effects on psychological well-being will also be explored as a secondary objective, serving as a proxy for the potential impact of the intervention.

**Methods:**

The study serves as a proof-of-concept investigation, where a small sample size (N=50) is deemed adequate to fulfill the study’s objectives. Participant recruitment will be conducted among pregnant women affiliated with the pregnancy care services of the Azienda Provinciale per i Servizi Sanitari di Trento, using a convenience sampling approach. ALBA will interact with the participating women for 6 weeks, between the 14th and 26th weeks of gestation. Specifically, there will be 1 session per week, which the woman can choose, to allow more flexibility regarding her needs, supplemented by ALBA-supported exercises to be performed between sessions. This study adopts a mixed methods approach, combining quantitative and qualitative data collection and analysis. Usability and engagement are assessed using the System Usability Scale, Chatbot Usability Questionnaire, User Engagement Scale-Short Form, and the User Mobile Rating Scale. Moreover, other quantitative outcome measures include levels of stress, anxiety, depression, emotional regulation, psychological flexibility, coping strategies, self-efficacy, and overall well-being, along with qualitative data from semistructured interviews. Finally, the analysis of the data gathered in this study will primarily adopt descriptive statistics and a text mining approach, focused on evaluating the attainment of the study objectives and changes over experimental time.

**Results:**

The psychoeducational approach aims to yield notable outcomes regarding the usability and engagement of women with ALBA. Furthermore, an anticipated enhancement in psychological well-being and quality of life is expected.

**Conclusions:**

Existing literature indicates a preference among women in the perinatal period for online support, highlighting the potential of digital interventions to address barriers related to social stigma and seeking assistance. In this context, ALBA emerges as a valuable resource, providing consistent psychoeducational support for women throughout pregnancy.

**International Registered Report Identifier (IRRID):**

PRR1-10.2196/53891

## Introduction

### Overview

Despite the increasing awareness of mental health issues and concerted efforts, a significant proportion of individuals with poor mental well-being do not receive prevention actions or appropriate care [1,2]. This treatment gap is influenced by various factors, including financial constraints, limited availability of services, and societal stigma, particularly for populations susceptible to stressful situations [3,4], including pregnancy.

The pregnancy period is characterized by essential transformations in the woman, with relevant impact on her physical, mental, and social well-being. How a woman adapts to these changes can affect her quality of life (QoL) and psychological well-being. The literature highlights that various psychological symptoms can be commonly experienced during pregnancy, ranging from anxiety, stress, and depression [5-9].

To date, psychoeducational interventions that promote women’s psychological well-being during pregnancy are scarce and tend to focus primarily on subgroups of women with psychiatric symptomatology, such as perinatal depressive disorder [5,10]. Evidence of the effectiveness of psychological interventions targeting pregnant women is increasing [11], but access to support services still presents several challenges. A considerable proportion of women face geographic barriers, with specialized centers often far from their homes [12,13]. In addition, a shortage of qualified staff, such as psychologists, further limits access to specialized care [12,13]. The stigma associated with mental health problems can also prevent women from seeking psychological support in these circumstances [12,13].

The overall strategy adopted by the World Health Organization (WHO) for mental health promotion is based on principles of inclusiveness and scalability for the public and susceptible populations [14]. WHO promotes inclusive mental health by aligning with human rights, ensuring cultural sensitivity, engaging diverse stakeholders, providing accessible and tailored services, and addressing social determinants to reduce disparities [15]. Within this framework, special attention is paid to the potential role of digital technologies in promoting psychological well-being, as it can be an optimal solution [16]; women can access it from anywhere and at any time, thus remaining flexible to their needs and reducing barriers related to service availability, social stigma, and seeking help [17].

The study described in this protocol is in line with WHO strategies and aims to assess the acceptability and feasibility of an intervention delivered through digital tools to promote psychological well-being. To the best of our knowledge, the intervention, originally validated by WHO and named Self-Help Plus (SH+), has never been used on this study’s target population, pregnant women.

SH+ is a low-intensity intervention developed by a multidisciplinary and international working group [18-20]. This type of intervention is usually designed to be transdiagnostic, easily adaptable in different settings, deliverable by nonspecialists, and based on sound evidence-based psychological principles embedded in a self-help approach (guided or unguided). This approach has already been validated in various target populations such as health care workers, migrants, and refugees to promote psychological well-being and clinical interventions, demonstrating general levels of acceptability and potential effectiveness [20]. A first attempt was made to make the protocol web-based within the RESPOND (Improving the Preparedness of Health Systems to Reduce Mental Health and Psychosocial Concerns Resulting From the COVID-19 Pandemic) project, but the involvement of a human person, in the role of helper, was still necessary [21].

Cognitive behavioral therapy techniques, particularly those referring to third-generation therapy, are shown to be more suitable than other psychotherapeutic approaches to be transferred into low-intensity interventions delivered by nontraditional methods, such as eHealth applications. SH+ is based on the principles of acceptance and commitment therapy (ACT), a third-wave form of cognitive behavioral therapy [22,23], and is divided into 5 chapters that address 5 strategies for managing stress and promoting psychological well-being. The five chapters, later translated into sessions, are as follows: (1) grounding (mindfulness), (2) unhooking (defusion), (3) acting on your values (values-based behavioral activation), (4) being kind (gratitude), and (5) making room (acceptance).

In this study, “acceptability” refers to participants’ perceived appropriateness, satisfaction, and willingness to engage with the digital intervention, as captured through self-report measures of user experience (UX) and user engagement (UE), as well as through semistructured interviews. “Feasibility” is defined as the extent to which the digital delivery of the SH+ intervention can be successfully implemented in the target population, considering aspects such as ease of access, completion rates, and usability. Both constructs are aligned with widely accepted definitions in the implementation science literature [24,25].

In conclusion, this study protocol aims to make the virtual coach, ALBA (A Well-Being Assistant), platform (described in the following paragraphs) available to women by evaluating the acceptability and feasibility of delivering SH+ through an assistant created to deliver psychoeducational sessions through dialogues, video, audio, and images (ie, the 5 chapters of SH+), as well as representing a virtual coach who guides the user in carrying out assigned exercises and tasks to be done independently between sessions. Moreover, we acknowledge that not all individuals who give birth identify as women, and that the more inclusive term would be “birthing person.*”* However, because most cases involve women, we have chosen to use the term *women* in this context. When specifically referring to birthing persons, appropriate linguistic and content-related considerations will be applied. Nevertheless, future replications of this intervention may be revised to ensure greater inclusivity.

### Goal of the Study and Research Questions

#### Overview

This study is positioned within the design and development cycle of the obesity-related behavioral intervention trials (ORBIT) model [26], specifically the refine phase. It involves delivering material based on SH+ in text, audio, and video formats by a virtual coach (ie, a digital assistant, identified as ALBA) implemented within the TreC Ricerca (TreC Research) app.

This intervention is embedded into the framework of behavior change interventions [27], which aim to enable women to acquire adaptive strategies to improve or maintain their psychological well-being. It should be noted that the term intervention in this context is used to identify a tool (in this case, the virtual coach) that will periodically be offered in a predefined (ie, rule-based), structured, and ordered manner, as informational material that has been structured and reviewed by psychological professionals.

This intervention has been developed and implemented for research purposes. The final goal is to validate the digital health intervention targeting women’s psychological well-being during pregnancy by helping them manage stressful situations more effectively through modules based on the principles of ACT.

#### Primary Objectives

The primary objectives of this proof-of-concept study described in this protocol paper are as follows: (1) to exploratively investigate through self-report standardized questionnaires UX and UE, that is, women’s experience and engagement when interacting with the TreC Ricerca app and the virtual coach, ALBA, (refer to the Step 3: Participation section for detailed description of questionnaires) and (2) to assess the women’s UE with ALBA and the app through semistructured interviews and investigate their feelings and overall experience during the intervention.

#### Secondary Objective

The secondary objective is to assess the level of pre-post psychological well-being through administered self-report questionnaires at the beginning and the end of the intervention.

This represents a preliminary exploration of the potential impact of the intervention by assessing changes in psychological well-being through post self-report questionnaires administered at the beginning and end of the intervention. Although this does not constitute an efficacy evaluation per se, it aligns with the *refine* phase of the ORBIT model, where early signals of potential effectiveness may be explored alongside feasibility and acceptability. This preliminary assessment aims to inform the design of future pilot or randomized controlled trials.

### ALBA Intervention

#### Overview

The virtual coach, ALBA, will deliver an intervention based on ACT techniques to promote QoL and perceived psychological well-being and manage stressful situations for pregnant women. The module is self-administered and available for both Android (Google LLC) and iOS devices (Apple Inc). All the contents of the dialogues were developed by a group of researchers affiliated with the Digital Health Research of the Bruno Kessler Foundation of Trento (Fondazione Bruno Kessler, Trento [FBK]) and psychologists from the Istituto Pavoniano Artigianelli with specific communication skills, based on the SH+ manual [28]. Subsequently, materials have been revised by a psychologist from the psychology operating unit of the Azienda Provinciale per i Servizi Sanitari di Trento (Provincial Health Services Authority of Trento; APSS). The dialogues, videos, and audio tracks were developed using an educational approach, rather than an emergency management approach. In addition, the structuring of the material and delivery methods was supervised by professionals from the WHO Center for Research in Mental Health at the University of Verona, who have already carried out implementation and validation studies of SH+ nationally and internationally.

To ensure the best possible adaptation of the intervention to our target sample, we previously conducted a co-design study based on guidelines of a previous step of the ORBIT model [26]. This process involved domain experts, such as psychologists, SH+ experts, communication and usability experts, and a small sample of new mothers and clinicians (midwives and gynecologists). For further details, please refer to our previous study [29].

#### Technological Tools

The technological component of the study is based on TreC. This platform allows citizens of the Autonomous Province of Trento to access, manage, and share information on their health and well-being [30]. TreC stands for *cartella clinica del cittadino* (citizen’s medical record) and is a reliable and well-tested platform designed to be a “system of systems” rather than a simple data hub. The central pillar of the TreC platform is the role of the citizen or as the manager of their health-related data, as in the case of a personal health record. TreC is designed with a flexible architecture, which enables the collection and management of heterogeneous data and allows the development and use of further subsystems to provide additional and specific functions.

This research project uses an additional module of the TreC platform, TreC Ricerca. The app can be downloaded via a specific link sent directly to participants. Authentication should be carried out via 2-factor authentication (one-time password code), which is secure and General Data Protection Regulation–compliant.

#### SH+ Sessions

SH+ intervention lasts 6 weeks, with 1 session of approximately 40 per week, which can be divided into 2 subsessions of 20 minutes each. Figure 1 shows a graphical representation of the conversational protocol delivered to women and its chronological structure.

**Figure 1 figure1:**
[figure not shown]
Graphical representation of the conversational protocol delivered to women and its chronological structure. COPE-NVI-25: Coping Orientation to the Problems Experienced–New Italian Version (25-item); ERQ: Emotion Regulation Questionnaire; GHQ: General Health Questionnaire; GSE: General Self-Efficacy Scale; ITA BUS B: Italian version of the Chatbot Usability Scale (version B); K10: Kessler Psychological Distress Scale; MPFI: Multidimensional Psychological Flexibility Inventory; PSS: Perceived Stress Scale; SF-36: 36-Item Short Form Health Survey; SH+: Self-Help Plus; SUS: System Usability Scale; UES-SF: User Engagement Scale-Short Form; uMARS: User Mobile Application Rating Scale; UX: user experience.

This intervention aims to enable women to acquire healthy coping strategies in stressful situations to promote psychological well-being during and after pregnancy.

The intervention was developed by referring to the SH+ program and adapting it to a psychoeducational course delivered via a virtual coach (refer to Figure 2 for some examples). The contents are presented through a gradual path that will enable the woman to become aware of herself and the present moment, accept and normalize internal states, cope with stress, and perceive an increase in her psychological well-being. In addition, the woman will be asked to perform tasks independently and fill out her diary daily.

**Figure 2 figure2:**
[figure not shown]
Mockups of the coach, ALBA (A Well-Being Assistant), within the TreC Ricerca app with some of its different sections.

## Methods

### Design and Study Plan

ALBA is designed to interact with pregnant women for 6 weeks, starting between weeks 14 and 26 of pregnancy. This period was chosen because the risk of miscarriage was much lower [31], a factor that could, of course, affect stress levels [32]. This will also ensure that we can complete the study before the due date of the participants. Weekly sessions are followed by the virtual coach’s instructions to independently perform some simple exercises and fill in the personal diary. The woman can choose the best day and time to interact with ALBA and perform exercises.

At the beginning of the pathway, ALBA will administer 6 self-report questionnaires, described in the Data Collection section, to establish a baseline for the examined psychological variables. After the data collection phase, the module will be administered, and its contents will be presented in different formats (ie, text, images, audio, and video).

An additional round of questionnaire administration is foreseen at the end of the intervention to assess potential changes in terms of psychological well-being and QoL perceived by the women. Four questionnaires will be administered to assess usability. To ensure the collection of all the necessary data, reminders were scheduled to complete the questionnaires 24, 48, and 72 hours after the first request. However, at present, there are no reminders for session completion.

Two months after giving birth, women from whom consent has been obtained will be invited to a semistructured interview to discuss their experience using ALBA and the app and to collect a more in-depth understanding of their experiences during the psychoeducational process. The 2-month postpartum period was chosen for both organizational convenience and methodological considerations. The expert group identified this timeframe to find a balance between scientific appropriateness and practical arrangements of the interviews, avoiding a prolonged span after the end of the intervention while ensuring that interviews with the participants were not conducted too close to the week of childbirth. The underlying assumption is that the period immediately following childbirth may be a logistically and emotionally complex time for the family, with a particular focus on the mother’s availability and experience.

### Participant Recruitment and Withdrawal

Recruitment will occur within the group of pregnant women between the 14th and 26th weeks of gestation attending the pregnancy care services of the APSS in Trentino.

Midwives from the APSS hospital and territorial service were involved in the study to identify women potentially eligible to participate.

The inclusion and exclusion criteria for women to participate in the study are provided in Textbox 1.

Figure 3 shows a flowchart of the research project procedure.

Inclusion and exclusion criteria.
**Inclusion criteria**
Be pregnantBe in a gestational state between the 14th and the 26th weekBe aged ≥18 yearsHave a smartphone with internet access, be able to download the app, and be able to use itBe a resident of the Autonomous Province of TrentoKnow and understand the Italian languageHave a stress level score, as measured by the Kessler Psychological Distress Scale, between 15.9 and 29.9Have a general well-being score, as measured by the General Health Questionnaire, ≥3Obtain a score on the Mental Health scale of the 36-Item Short Form Health Survey between 30 and 80.
**Exclusion criteria**
Patients unable to provide informed consent, which is a prerequisite for participation in the studyInadequate understanding of the Italian languageSubstance addiction or in recovery for 1 yearSuicidal tendenciesDepression or other psychiatric diagnosesWomen undergoing medically assisted procreation (due to the increased risk of anxiety and depressive states, ascertained in the literature)Already being placed, followed, or taken care of on a psychological or psychotherapeutic path at the time of recruitment

**Figure 3 figure3:**
[figure not shown]
Flowchart of the research project procedure. ALBA: A Well-Being Assistant.

### Sample Size

This research project is designed as a proof-of-concept study, where a limited sample is sufficient to achieve the intended aims. It was calculated that if nonparametric statistics are conducted (assuming the distribution is not normal), the sample should consist of 24 pregnant women with Bonferroni correction (α=.025). The sample size and power for nonparametric tests (Kruskal-Wallis and Wilcoxon post hoc tests) were calculated according to method reported by Noether [33]. If parametric statistics are conducted (assuming the normal distribution), the sample should consist of 41 pregnant women with Bonferroni correction (α=.025). The sample calculation was further confirmed with the

Power Analysis and Sample Size (NCSS LLC) and Stata (StataCorp LLC) programs, for which the resulting numerosity is 41 participants, assuming null hypothesis (Ho):d=d0, alternative hypothesis (Ha):d≠d0, and considering as study parameters α=.025; mean of group 1 (ma1): 0.000; power: 0.800; mean of group 2 (ma2): 1.000; delta (difference of means, delta): 0.500; expected difference (da): 1.000; and SD of difference (sd_d): 2.000.

Thus, by a power level set at 0.80, a significance level of .025, and considering a 20% potential dropout rate, an estimated 50 pregnant women are needed for recruitment to conduct the study.

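### The nonparametric sample size of 24 does not follow from the only effect stated (difference 1, SD 2, two-sided α=.025, power 0.80), and Kruskal-Wallis does not fit a single-arm pre-post design

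*Protocol article*

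**What the plan says.** The Sample Size section of the protocol article gives two figures at a Bonferroni-corrected α of .025. If the distribution is assumed not normal, "the sample should consist of 24 pregnant women with Bonferroni correction (α=.025"). The basis given is that sample size and power for "nonparametric tests (Kruskal-Wallis and Wilcoxon post hoc tests) were calculated according to method reported by Noether". If normality is assumed, "the sample should consist of 41 pregnant women with Bonferroni correction (α=.025"). 

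The section then lists the inputs behind its software confirmation of 41: a two-sided test ("alternative hypothesis (Ha):d≠d0"), power 0.80, α .025, and "delta (difference of means, delta): 0.500; expected difference (da): 1.000; and SD of difference (sd_d): 2.000". No separate effect size, probability or distribution is given for the 24.

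Recruitment is set from these figures: "considering a 20% potential dropout rate, an estimated 50 pregnant women are needed for recruitment to conduct the study".

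The Quantitative Analysis section plans paired tests (paired t, Wilcoxon, sign test) of beginning against end in the same women, chosen by whether assumptions are met. The Limitations section says that no control group is planned.

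**The concern.** At the same α, the rank-test figure is about 40% below the t-test figure (24 against 41). If both answer the same question for the same effect, a gap of that size in that direction needs an explanation, and none is given. The test family named for the 24 includes one for independent groups, which suggests that the formula was not applied to the paired design.

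The pre-post comparison is a secondary objective, but it matters: the Results section lists significant improvement in psychological measures among the benchmarks for moving to a broader trial. The Wilcoxon test is the planned fallback when assumptions fail. If retention were poor, the sentence giving 24 could be cited to claim adequate power that the stated effect does not support, and a later trial could inherit the figure.

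**Working it through.** **Inputs (Sample Size section).** Mean paired difference 1.0 and SD of differences 2.0, so d = 1.0/2.0 = 0.5; two-sided α = .025; power 0.80; 20% dropout; 50 recruited. Normal quantiles: z(0.9875) = 2.241 and z(0.80) = 0.842, so (2.241 + 0.842)² = 9.505.

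**1. The 41.** Paired t-test power from the noncentral t distribution, with n − 1 degrees of freedom and noncentrality 0.5√n: 0.793 at n = 40 and 0.805 at n = 41. The stated 41 reproduces.

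**2. The 24, by Noether's signed-rank formula.** n = (z_α + z_β)² / [3(p′ − 0.5)²], where p′ is the probability that the sum of two independent differences is positive. The article does not give p′. If differences are normal, p′ = Φ(0.5·√2) = 0.760, and n = 9.505 / (3 × 0.260²) = 46.8, so 47.

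**3. The same by simulation.** Normal differences, 40,000 runs, exact signed-rank critical values. Power is 0.51 at n = 24, 0.798 at n = 42 and 0.809 at n = 43, so 42–43 women are needed.

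**4. Other readings of the inputs.** At d = 0.5 and α = .025, the sign test needs 64.8, so 65. One-sided .025 gives 39 for the signed-rank test, and one-sided .05 gives 31. Solving Noether's formula for n = 24 gives p′ = 0.5 + √(9.505/72) = 0.863, or d ≈ 0.77. The only route found to 24 is Noether's two-sample formula at a 1-SD shift: p = Φ(1/√2) = 0.760, total 9.505 / [12 × 0.25 × 0.260²] = 46.8, which is 23.4, so 24, per group. That uses two independent groups and does not divide the difference by its SD of 2. As an account of where the 24 came from, it is an inference.

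**5. Non-normal differences.** The 24 is tied to non-normality, so signed-rank power was also simulated for assumed shapes with mean 1 and SD 2. The shapes are not the protocol's. Values are approximate.

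| Shape of differences | n = 24 | n = 40 |
|---|---|---|
| Normal | 0.51 | 0.78 |
| Exponential, long tail in the direction of effect | 0.40 | 0.66 |
| Uniform | 0.45 | 0.72 |
| t, 5 df | 0.61 | 0.86 |
| Laplace | 0.65 | 0.88 |
| Exponential, long tail against the effect | 0.68 | 0.90 |
| t, 3 df | 0.78 | 0.95 |

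No shape reaches 0.80 at n = 24.

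**6. Dropout.** 50 × 0.80 = 40 completers. The target matches 41 × 1.20 = 49.2, so 50; dividing gives 41 / 0.80 = 51.25, so 52. Keeping 41 of 50 allows a loss of 9/50 = 18%.

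**The case against.** The strongest reply is that the article attaches the 24 to non-normal data and prints no input for it; the parameter list belongs to the 41. Under heavy tails a signed-rank test can need fewer women than the t-test, so 24 being below 41 is not in itself an error. This stands as far as it goes. A reader might infer that a rank test can never need fewer women than a t-test, and the documents do not support that. It does not rescue the 24, however: the stated effect is the only one available, and even the t distribution with 3 degrees of freedom falls just short at n = 24. A condensed article may leave detail to the full protocol, but here it prints a number beside an effect that does not produce it.

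A reader might also infer that 50 recruits fall short for whichever test is used. That is too strong. For the t-test the shortfall is one woman and less than one percentage point of power. For the signed-rank test it depends on shape: 40 completers give less than 0.80 if differences are normal, but 0.86–0.95 under the heavy-tailed shapes.

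Finally, the consequence is limited. The target was set from 41, so the 24 lowered nothing. The Secondary Objective section calls the pre-post comparison a preliminary exploration, not an efficacy evaluation. That bears on weight; it does not make the figure right.

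**Conclusion.** The point holds for the 24. It does not reproduce from the stated effect, where 47 (Noether) or 42–43 (simulation) are needed if differences are normal. Power at 24 is about 0.51 under normality and about 0.40–0.78 under the non-normal shapes tried. This rests on taking d = 0.5 as the effect for both figures, since the article gives no other, and on assumed shapes. Another effect or a more extreme distribution could yield 24, but neither is stated.

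The Kruskal-Wallis reference is inconsistent with the single-arm, paired design and with the article's own list of planned tests. The dropout arithmetic is a minor slip, from multiplying by 1.2 instead of dividing by 0.8, and is not a material error for the t-test. None of this shows that the study is too small for its feasibility aims or that recruitment must rise.

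**What to change.** In the Sample Size section, delete the figure 24 and the reference to Kruskal-Wallis. Alternatively, keep 24 and state the probability and the distribution of differences under which it holds for the paired signed-rank test.

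Then state what 50 delivers, with the assumption attached: 50 recruited with 20% loss gives 40 completers. For d = 0.5 at two-sided α = .025, that is 79% power for the paired t-test and about 78% for the Wilcoxon signed-rank test if differences are normal (about 66–95% under other assumed shapes). Or state the tolerable loss for the t-test as 18% (9 of 50).

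The cost is one rewritten paragraph and a stated power just under 0.80. No additional women and no design change are needed.
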